### Outcome measures

The primary endpoint is defined as change in the Reactive Hyperemia Index (RHI) at 12 months. Secondary endpoints included changes in the right and left maximum IMT of the CCA and internal carotid artery (ICA), mean IMT of the CCA and ICA at 24 months, and 24-month cardiovascular events including cardiac death, stroke, acute myocardial infarction (AMI), overall cause of death, withdrawal of drug, or bleeding events.

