### Procedures

Measurement of PAT ratio will be performed with the standard technique and device [11–14]. Endo-PAT measurements will be performed at baseline and at 12 months after randomization. The RH-PAT 2000 device (Itamar Medical, Caesarea, Israel) will be used for digital RH-PAT to evaluate endothelial function as previously described. The RH-PAT Index (RHI) reflects the extent of reactive hyperemia and is calculated as the ratio of the average amplitude of PAT signal over 1 min starting 1.5 min after cuff deflation (control arm, A; occluded arm, C) divided by the average amplitude of PAT signal at the 2.5-min time period before cuff inflation (baseline) (control arm, B; occluded arm, D). Thus:$$ RHI = \left(C/D\right)/\left(A/B\right) \times \mathrm{baseline}\ \mathrm{correction}. $$

Impaired endothelial function is defined as a log RHI less than 0.6, and favorable endothelial function is defined as a log RHI more than or equal to 0.6.

Measurement of CCA-IMT will be performed with the standard technique and device [12, 15]. Imaging studies of the left and right carotid arteries will be performed by expert sonographers who are well-trained in the use of 10-MHz linear vascular probes (Vivid 7, GE Vingmed Ultrasound, Horten, Norway). Measurements will be performed at baseline, and at 12 months and 24 months after randomization. To avoid interobserver variability, the same investigator will examine each participant with the same equipment throughout all the visits. The IMT will be measured as the distance between two parallel echogenic lines corresponding to the blood-intima and media-adventitia interface on the posterior wall of the artery. Three IMT determinations will be performed at the site of the thickest point with a maximum CCA-IMT and two adjacent points (1 cm upstream and 1 cm downstream from this site). These three determinations will be averaged (mean CCA-IMT). The CCA is defined as the segment extending from 10 to 20 mm proximal to the tip of the common carotid bifurcation site. The ICA is defined as the segment 10 mm distal to the tip of the common carotid bifurcation site, and the bifurcation is defined as the segment between the CCA and the ICA. Carotid IMT will be measured using dedicated software (Intimascope, Media Cross Co., Tokyo, Japan) by an examiner blinded to all clinical information.

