### Sample size measure and statistics

This study is a prospective, pilot study for a proof of concept trial. In a previous studies, the RHI was 1.63 ± 0.28 in patients with permanent/persistent AF [13, 14]. We assume that NOAC will improve RHI values by an 8 % difference with no significant difference between the two different NOACs. The expected difference in RHI was driven from clinical significances and previous medical treatments in other study population [16–18]. To detect a statistically significant difference with a power of 80 % with a two-sided *α*-level of 0.05, a sample of 165 patients (55 patients for each group) will be required. Assuming dropout rates would be 20 %, the total sample size will be set at 198 subjects.

Statistical analyses will be carried out using the SPSS Statistics for Windows ver. 17.0 software package (SPSS Inc., Chicago, IL, USA). A two-sided *p* < 0.05 is considered significant. Continuous variables, presented as means ± standard deviations, will be evaluated for normal distribution and compared using the Student *t* test or analysis of variance test accordingly. The continuous parameters with a skewed distribution will be logarithmically transformed and categorical variables, presented as frequencies and percentages, will be compared using the chi-square test or Fisher’s exact test when appropriate. Repeated measures parameters over time between the groups will be determined by repeated measure analysis of variance with an autoregressive model or analysis of covariance adjusting for baseline values. The clinical event rates will be assessed using the Kaplan-Meier method and the log-rank test will be used to compare survival between the two groups and the Cox proportional hazards model will be used for multivariate analysis (forward stepwise) to investigate which of the parameters identified using univariate analysis are significantly associated with clinical events.

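### The 24-month carotid IMT change may be analysed with an autoregressive model that can misstate its standard error; one less restrictive method should be fixed in advance

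*Protocol article*

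**What the plan says.** In the protocol article, the section on sample size and statistics gives two options in one sentence: "Repeated measures parameters over time between the groups will be determined by repeated measure analysis of variance with an autoregressive model", followed by "or analysis of covariance adjusting for baseline values". It does not assign either option to an endpoint. It also leaves open the order of the autoregression and whether variances are equal across visits.

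The Procedures section sets the IMT schedule: "Measurements will be performed at baseline, and at 12 months and 24 months after randomization". Outcome measures lists IMT change as secondary: "Secondary endpoints included changes in the right and left maximum IMT of the CCA and internal carotid artery (ICA), mean IMT of the CCA", with the time point given in "mean IMT of the CCA and ICA at 24 months". The working hypothesis, under Study subjects and hypothesis, also covers progression of common carotid IMT at 12 and 24 months.

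The primary endpoint differs in kind. "The primary endpoint is defined as change in the Reactive Hyperemia Index (RHI) at 12 months", and "Endo-PAT measurements will be performed at baseline and at 12 months after randomization", so it has two visits only.

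**The concern.** IMT is the only listed endpoint with three scheduled measurements, so it is where a serial-correlation structure has consequences. A first-order autoregressive model has one correlation parameter. Once the correlation between adjacent visits is fitted, the 0–24 month correlation is fixed at its square, whatever the data show. The 24-month contrast uses exactly that correlation.

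The model also attributes all loss of correlation to elapsed time and has no term for reading error at each visit. A stable patient level plus reading error gives nearly constant correlation, and the model then makes the standard error too large. Real differences between patients in rate of progression push the other way. At stake is the IMT part of the working hypothesis: a true slowing of progression could be missed or, less probably on the scenarios tried, a chance difference could be declared too often.

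The text also permits two analyses of the same IMT data that can differ appreciably in power, with no stated rule for choosing between them.

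**Working it through.** **The plan's own figure.** The only sample size concerns RHI: "the RHI was 1.63 ± 0.28 in patients with permanent/persistent AF", an 8% improvement, 80% power, two-sided 0.05. The difference is 0.08 × 1.63 = 0.1304. For pooled NOAC against warfarin (2:1), the warfarin arm needs (1 + 1/2) × (0.28/0.1304)² × (1.960 + 0.842)² ≈ 54.3, so 55, and 165 in total, as stated. No power, effect, SD or correlation is given for IMT, so there is no IMT figure to reproduce.

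**Assumptions for IMT.** First-order autoregression; equal variance σ² at each visit in the first table; complete data; free group-by-visit means; and a true effect that a test with the correct standard error detects with 80% power.

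**Step 1: what the model estimates.** With three equally spaced visits, the inverse of the autoregressive matrix has no 0–24 month element, so the likelihood ignores the observed 0–24 month covariance. When both adjacent correlations equal r and variances are equal, the fitted correlation is r.

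**Step 2: ratio of standard errors.** Write r24 for the true 0–24 month correlation.
- True variance of the 24-month change: 2σ²(1 − r24)
- Variance under the model: 2σ²(1 − r²)
- Ratio k = √[(1 − r²)/(1 − r24)], which is √(1 + r) under constant correlation

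**Step 3: power and type I error.** Power = 1 − Φ(1.960k − 2.802); type I error = 2[1 − Φ(1.960k)].

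Example with r = r24 = 0.8: the variances are 0.40σ² (true) and 0.72σ² (model), so k = √1.8 = 1.342. The effective critical value is 1.960 × 1.342 = 2.630. Power is 1 − Φ(−0.172) = 56.8%, and type I error is 0.9%.

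| True correlation, 12 / 24 months | k | Power | Loss (points) | Type I error |
|---|---|---|---|---|
| 0.5 / 0.5 | 1.22 | 65.6% | 14.4 | 1.6% |
| 0.6 / 0.6 | 1.26 | 62.6% | 17.4 | 1.3% |
| 0.7 / 0.7 | 1.30 | 59.7% | 20.3 | 1.1% |
| 0.8 / 0.8 | 1.34 | 56.8% | 23.2 | 0.9% |
| 0.9 / 0.9 | 1.38 | 54.0% | 26.0 | 0.7% |
| 0.8 / 0.75 | 1.20 | 67.4% | 12.6 | 1.9% |
| 0.8 / 0.70 | 1.10 | 74.4% | 5.6 | 3.2% |
| 0.9 / 0.85 | 1.13 | 72.4% | 7.6 | 2.7% |
| 0.7 / 0.6 | 1.13 | 72.2% | 7.8 | 2.7% |
| 0.8 / 0.64 (geometric) | 1.00 | 80.0% | 0 | 5.0% |

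With 90% reference power, the losses under constant correlation of 0.5 to 0.9 are 10 to 20 points.

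**Step 4: patient level, slope and reading error.** The SDs are assumed. The true variance of the 24-month change is 4 × slope SD² + 2 × error SD²; the model variance comes from the best-fitting autoregressive matrix.
- Level 0.17 mm, slope 0.025 mm/year, error 0.06 mm: true 0.0025 + 0.0072 = 0.0097, model 0.0147, k = 1.23, power 65%.
- Level 0.17 mm, slope 0.04 mm/year, error 0.03 mm: true 0.0064 + 0.0018 = 0.0082, model 0.0066, k = 0.90, type I error 7.8%.

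**Step 5: simulation and alternatives.** Simulated power with 55 per arm and 2,000 replicates:

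| True correlation | Autoregressive | Unstructured | Baseline-adjusted ANCOVA |
|---|---|---|---|
| 0.7 / 0.7 | 59.6% | 80.6% | 86.0% |
| 0.8 / 0.8 | 57.8% | 80.2% | 83.6% |
| 0.9 / 0.9 | 55.2% | 80.9% | 82.2% |
| 0.8 / 0.75 | 65.3% | 78.2% | 83.6% |
| 0.9 / 0.85 | 70.2% | 78.5% | 81.6% |
| 0.8 / 0.64 | 80.2% | 79.8% | 87.0% |

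**Step 6: primary endpoint.** With two visits there is only one correlation, so the structure imposes nothing on the RHI change.

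**The case against.** The strongest reply is that the sentence does not commit IMT to the autoregressive model. It lists ANCOVA adjusted for baseline as an alternative, and ANCOVA of the 24-month value has no serial-correlation structure. It names no endpoint and no order of autoregression, and it does not say that the 24-month contrast would be read from the autoregressive fit. An article may leave such detail to an analysis plan. IMT is a secondary endpoint with no stated power in a study that calls itself a pilot, and where correlation decays more slowly than geometrically the error is conservative.

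Most of this stands, and it limits the point. A reader might infer that the 24-month IMT test has the wrong standard error. The document does not support that: the model is one of two options, and its standard error is wrong only if the true correlations depart from geometric decay. A reader might also take a loss of 20 to 25 points as the expected size. That needs near-constant correlation of about 0.7 or more and 80% reference power, close to the top of the range. Using the same investigator and equipment for each patient, as Procedures requires, reduces reading variation but does not show that correlation stays constant over two years.

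What the reply does not remove is that the article itself names the autoregressive structure as a permitted analysis, so this is stated text and not an omission. The alternative beside it helps only if it is the one chosen, and the article gives no rule for that.

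**Conclusion.** The point holds as a conditional weakness in a secondary analysis. If the autoregressive option is used for the 24-month IMT change in its usual form, its standard error is right only under geometric decay. Power loss then runs from 0 to about 26 points against an 80% reference, and type I error from about 0.7% to about 8%. Neither direction nor size can be settled from the article, which gives no IMT correlations or SDs. The figures also assume first-order, equal-variance autoregression and complete data. The primary 12-month RHI comparison is untouched. This is a cheap improvement to a stated method and not a demonstrated error.

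**What to change.** For the 24-month IMT change, drop the autoregressive option and fix one method before 24-month data exist. Either would serve:

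- a repeated-measures mixed model with unstructured covariance over the three visits, reading the treatment effect from the 24-month change contrast; or
- the baseline-adjusted ANCOVA already listed, applied to the 24-month value.

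The cost is one sentence, with no extra patients, visits or measurements. The unstructured matrix has six covariance parameters against two for the equal-variance autoregressive form, which 165 to 198 patients can support. Loss of precision is negligible: when the autoregressive pattern is true, simulated power is 79.8% unstructured against 80.2% autoregressive.

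### The sample size for change in RHI uses a single-visit SD, and the plan does not choose between repeated-measures ANOVA and the more precise baseline-adjusted ANCOVA

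*Protocol article*

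**What the plan says.** Under Outcome measures: "The primary endpoint is defined as change in the Reactive Hyperemia Index (RHI) at 12 months". Under Procedures, RHI is scheduled twice: "Endo-PAT measurements will be performed at baseline and at 12 months after randomization".

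Under Sample size measure and statistics, the planning value is a cross-sectional level: "the RHI was 1.63 ± 0.28 in patients with permanent/persistent AF". The effect is stated as "We assume that NOAC will improve RHI values by an 8 % difference with no significant difference between the two different NOACs". Power is set at 80% with a two-sided 5% test, which gives 55 patients per group (165), raised to 198 for 20% dropout.

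The same section says that repeated measures will be compared between groups by "repeated measure analysis of variance with an autoregressive model or analysis of covariance adjusting for baseline values". It also lists the t test or ANOVA for continuous variables in general. No sentence ties one of these methods to RHI, and none gives an SD of change or a correlation between the two readings.

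**The concern.** The spread of a change is not the spread of one reading. With equal SDs at both visits, the SD of change is 0.28 × sqrt(2(1 − rho)), which equals 0.28 only when rho is 0.5. For a change-score analysis, the stated 80% therefore rests on a correlation that the text does not mention.

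The two methods joined by the plan's "or" are also not interchangeable. One subtracts the baseline in full; the other adjusts for it by regression and is at least as precise at every rho. While the choice is open, the power of the primary test is undefined and the test could be picked after the data are seen. The Discussion acknowledges that the trial is not double-blind, which is one more reason to settle the choice in advance.

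**Working it through.** **Inputs.** Mean RHI 1.63, SD 0.28, difference 8%, power 80%, two-sided alpha 0.05, 55 per group (Sample size measure and statistics); 1:1:1 allocation (Randomization and allocation concealment); RHI at two visits (Procedures). Rho is not given, so a range is shown. The SD is assumed equal at both visits.

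**Step 1: reproduce the plan's figure.** The difference is 0.08 × 1.63 = 0.1304. With the two NOAC arms pooled against warfarin (2:1), the warfarin arm needs

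n = 1.5 × (0.28 × (1.960 + 0.842) / 0.1304)² = 54.3, rounded up to 55, total 165.

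This matches exactly. Other readings do not: a two-sided comparison of one NOAC with warfarin needs 73 per arm, a one-sided one needs 58, and a three-group F test needs 204 in total. The calculation therefore used the single-visit SD of 0.28 and the pooled contrast.

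**Step 2: what the repeated-measures option tests.** With two visits an autoregressive structure has a single correlation, and the group-by-time test is the comparison of mean change between groups, without adjustment for baseline.

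**Step 3: SD under each option.**

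- Change score: 0.28 × sqrt(2(1 − rho))
- ANCOVA: 0.28 × sqrt(1 − rho²)
- Ratio of variances, ANCOVA to change score: (1 − rho²) / (2(1 − rho)) = (1 + rho)/2

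**Step 4: power at 110 vs 55, difference 0.1304, non-central t.**

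| rho (assumed) | SD of change | Power, change score | ANCOVA SD | Power, ANCOVA |
|---|---|---|---|---|
| 0 | 0.396 | 50.9% | 0.280 | 80.1% |
| 0.2 | 0.354 | 60.1% | 0.274 | 81.6% |
| 0.3 | 0.331 | 65.9% | 0.267 | 83.6% |
| 0.4 | 0.307 | 72.5% | 0.257 | 86.4% |
| 0.5 | 0.280 | 80.1% | 0.242 | 89.9% |
| 0.7 | 0.217 | 95.1% | 0.200 | 97.5% |

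For 80% power, the change score needs (normal approximation) 261 evaluable patients at rho 0.2, 228 at 0.3, 198 at 0.4 and 165 at 0.5.

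**Step 5: how far the ANCOVA figures carry.**

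- *Dropout.* 198 less 20% leaves about 158 evaluable. ANCOVA power on the raw scale is then 78.4% at rho 0 and 80.0% at 0.2.
- *Log scale.* If RHI is taken as lognormal, the log SD is sqrt(ln(1 + (0.28/1.63)²)) = 0.1705 and the effect is ln 1.08 = 0.0770. ANCOVA power at 110 vs 55 is 77.5% at rho 0, 79.2% at 0.2 and 81.3% at 0.3. With 158 evaluable it is 75.8%, 77.5% and 79.7%.
- *One NOAC against warfarin (55 vs 55), raw scale.* ANCOVA power is 67.7% at rho 0 and about 80% at rho 0.5.

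**The case against.** The strongest reply is that no underpowering has been shown. The document gives no rho. At 0.5 the change score has the stated power and above 0.5 it has more. That stands: the 60% to 73% figures depend on assumed correlations of 0.2 to 0.4.

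It can also be said that this is a condensed article about a pilot, proof-of-concept trial, that model details belong in a fuller document, and that ANCOVA is already one of the two listed options. No invalid analysis is prescribed, and that stands too. A plain comparison of 12-month values, which the general t test or ANOVA wording could cover, would also keep about 80%. But the article does more than stay silent. It offers two methods with different power for an endpoint that it defines as a change, and it sizes the trial with an SD that fits the change score at only one value of rho.

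A reader might infer several stronger points that the documents do not support:

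- *That ANCOVA secures 80% at any correlation.* It does so only on the raw scale, for the pooled contrast, with all 165 evaluable (Step 5).
- *That the plan would test the group main effect, which averages in the baseline visit.* The plan names no such test; comparing measurements over time between groups points to group-by-time.
- *That the rule "continuous parameters with a skewed distribution will be logarithmically transformed" cannot work for a change, which may be negative.* The natural reading is to log RHI at each visit, and Procedures already defines impairment on log RHI.
- *That the autoregressive structure spoils the IMT analysis.* That needs a correlation pattern over three visits that the document does not give, and the plan claims no power for IMT.

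**Conclusion.** The point holds as a no-cost improvement in precision and pre-specification. The 55 per group reproduces from the single-visit SD with the NOAC arms pooled, while the endpoint is a change and its primary analysis is left open. At rho 0.2, 0.3 and 0.5, ANCOVA gains about 21, 18 and 10 percentage points of power over the change-score test. Its variance is (1 + rho)/2 of the other, which is 40% lower at rho 0.2 and 25% lower at rho 0.5.

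These sizes assume equal SDs at both visits, the plan's own 0.28 and 8%, the pooled contrast and 165 evaluable patients. The pooled contrast is inferred from the sample size arithmetic and from the assumption of no difference between the NOACs; the article does not name it as the primary test. That the trial will miss 80% is not established. What is established is that the stated power belongs to a change-score analysis only if rho is about 0.5 or more, and the plan does not say so.

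**What to change.** For the primary endpoint, remove the "or" and name one analysis: ANCOVA of 12-month RHI on randomised group with baseline RHI as covariate, for pooled NOAC against warfarin. Fix the scale, raw or log, in advance; on the log scale the effect is a ratio, which fits an assumption stated as a percentage. Restate the power for that analysis and scale with its assumed SD, rho and number evaluable after dropout, accepting that it may fall slightly below 80% if rho is low.

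The cost is a few lines of wording and one recalculation. No visit or measurement is added. The article reports that recruitment is ongoing, so the choice can be recorded before the outcomes are analysed.

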## Discussion

The aim of this study is to determine the efficacy of NOAC therapy in the prevention of endothelial dysfunction and progression of atherosclerosis in AF subjects. Recent evidence suggests that AF adversely affects endothelial function [11, 13, 14]. Further, conversion of AF to sinus rhythm results in improved flow-mediated vasodilatation (FMD) in patients with persistent AF [13, 14]. It is not known whether the vitK antagonists are effective in affecting endothelial function and atherosclerotic progression in AF patients. Preclinical evidence shows that NOACs are effective in reducing inflammatory cytokines and atherosclerotic cascades [5–8]; however, clinical data are lacking. We believe that the therapeutic effects resulting from aspirin or warfarin and NOACs, which have different mechanisms of action, have not been sufficiently investigated in AF patients. The results of this study are expected to broaden our understanding of NOAC mechanisms in humans and lead to the development of appropriate drug therapies for patients with AF and atherosclerosis. This is a very important objective because the incidence of AF and its common complications are rising at a staggering rate in many countries.

One of the study limitations is that the primary outcome in this study is not a hard endpoint for clinical outcome but a surrogate marker for endothelial dysfunction. Therefore, further study for clinical outcome of vascular events comparing NOACs and warfarin should follow after this trial. Furthermore, this study is not double-blind trial. To minimize the bias, the technician performing examination and analysis will be blind to the allocation of patients.

### Trial status

This study is ongoing. We are currently recruiting and enrolling subjects at the Kyung Hee University Medical Center.

## Abbreviations

AF: Atrial fibrillation
AMI: Acute myocardial infarction
CCA: Common carotid artery
FMD: Flow-mediated vasodilatation
ICA: Internal carotid artery
IMT: Intima-media thickness
IRB: Institutional Review Board
NOAC: New oral anticoagulants
PAR: Protease-activated receptor
PREFER-AF: PREvention oF thromboembolic events – European Registry in Atrial Fibrillation
RHI: Reactive Hyperemia Index
RH-PAT: Reactive hyperemia peripheral arterial tonometry
